#### Participants

Following the recruitment of community organizations, all women who decide to attend the workshops will be self-identified for participation in the study. Recruitment strategies vary slightly per site, based on the requirements of the respective ethics committees. In France and in Western Canada, baseline data will be collected and participants will be screened and enrolled to the study prior to the receipt of the intervention. In the UK and Quebec, women will complete the baseline questionnaire prior to the delivery of the intervention, but interested participants will sign the consent form and return the baseline questionnaire only after the workshop is completed. In a second screening stage, a research assistant confirms eligibility status and interest in enrolling in the trial via telephone follow-up within 1 week of the workshop.

Across all sites, a subsample of participants will be recruited for an ethnographic study that aims to explore continence stigma, aging, and participant perspectives of the intervention and control workshops. Data from the qualitative interviews will help the team understand the mechanisms and outcomes of the intervention on self-stigma related to incontinence. Approximately 20 participants will be interviewed within 2 weeks of the workshop to explore participant perspectives of the intervention and control workshops, and related feelings associated with continence and age-related stigma. A second group of 20 participants will be interviewed 1 year after the intervention workshop. Five participants from each trial site will be purposively selected from those who have shown significant benefit from the continence promotion intervention, to investigate the impact on stigma and to understand the mechanisms behind the perceived benefits of the workshop.

### Randomization

#### Randomization/Concealment of allocation

Randomization will occur prior to delivery of the intervention. The unit of randomization will be the community organization. Using block randomization with an alternating block size of 2 or 4, we will randomly allocate clusters (via a 1:1 ratio and stratified by site) to the intervention or control group via a computer-generated random digit performed by an independent statistician (Fig. 2). Stratification by site will aim to account for any variation resulting from site characteristics and participants from individual community organizations. The trial is, nonetheless, considered open-label because both the research assistant who delivers the interventions and the study participants who will have received the interventions will be aware of group allocation at the time of implementation.

#### Blinding

The trial is blinded at the level of cluster randomization: community organizations are aware that their participants will receive one of the two interventions, but they will be blinded to group allocation. Participants will be aware of which intervention they receive as the intervention is open-label. A research assistant, who will be blinded to group allocation, will inform, deliver and complete the questionnaires after each telephone follow-up. A statistician blinded to the allocation will conduct the analysis and reporting of the co-primary outcome measures.

### Intervention

The continence promotion intervention is a single 45-minute interactive group continence promotion program delivered by a trained research assistant/workshop facilitator. The continence intervention incorporates constructivist learning and discusses the risk factors, causes and treatments for incontinence and challenges the misconception that incontinence is a normal part of aging. It aims to motivate community-dwelling women to initiate evidence-based self-management and/or to consult for treatment [26–30]. The intervention workshop is introduced as an educational workshop addressing “taboo” topics related to aging (memory problems and incontinence). Risk factors and different etiologies for incontinence are reviewed, physiology and pathology explained in lay terms and modifiable strategies for risk reduction are recommended. A paper-based self-management tool is provided at the end of the workshop to help participants monitor their symptoms before and after attempting evidence-based self-management strategies. This paper-based tool asks women to identify one of the risk factors they may have for urine leakage and to implement a strategy for risk reduction. This is the same intervention that was tested in the pilot trial [26].

The sham control intervention (the comparator) for this study is a single 45-minute interactive group workshop on other health topics of importance to older women. The topics discussed are memory problems, medication interactions, sleep problems, and hearing loss. Incontinence is mentioned briefly during the sham control intervention in order to integrate it with the questionnaire that revolves around bladder problems.

A fidelity protocol and checklist for delivery of the intervention will be applied every 6 months to each study site, in order to ensure standardized implementation of the intervention in each country.

### Study follow-up

Study follow-up will include five telephone calls. The first within a week of the workshop then at, 3, 6, 9 and 12 months post workshop. Telephone interviews normally last from 5 to 40 minutes.

#### Stigma and quality of life

The second co-primary outcome will be the difference in quality of life and stigmatization between the intervention and control groups. The 22-item Incontinence Quality of Life questionnaire (I-QOL) is a validated quality of life instrument for urinary incontinence that includes content relevant to stigma, such as “I worry about others smelling urine on me” and “I worry about being embarrassed or humiliated because of my incontinence” [33].

Exploration of stigma perceptions will be supplemented by the data collected in the qualitative interviews among a sub-group of participants immediately after, and at 1 year post intervention. Data will be collected using semi-structured one-to-one interviews. The qualitative investigation will also be used in the development of the Continence Psychosocial Impact of Assistive Devices Scale (C-PIADS), which is being developed from the original validated Psychosocial Impact of Assistive Devices Scale (PIADS). PIADS is a 26-item self-report questionnaire that includes 3 domains: competence (reflecting perceived functional capability, independence and performance); adaptability (reflecting inclination or motivation to participate socially and take risks); and self-esteem (reflecting self-confidence, self-esteem, and emotional well-being). This team is developing a modified version of this measure, C-PIADS that will evaluate the impacts of continence care product use on psychosocial constructs including perceived stigma [34, 35]. In addition to the original 26 items, the present version of the C-PIADS includes an additional 7 items, including self-consciousness, fear of being “outed,”’ social acceptance, secrecy, isolation, revealing to others, social participation and intimate relations. The C-PIADS will be administered on two occasions, after completion of the ethnographic interview, and on the telephone 1 week after the ethnographic interview.

#### Falls

The third co-primary outcome measure will be falls experienced by women exposed to the continence intervention compared to women exposed to the sham treatment 1 year postintervention. Falls will be measured as the group rate of falls at 12 months; the proportion of women who had a fall; and the proportion of injurious falls. Falls will be defined as an unexpected event in which the person comes to rest on the ground, floor or lower level [36]. Data for falls will be obtained from a falls diary with telephone reminders [37]. Previous work has shown that falls diaries pose significant advantage over other methods of capturing falls among older-aged people [37].

#### Incremental cost-effectiveness ratio and quality-adjusted life years

We will conduct both cost-effectiveness and cost-utility analysis (CEA and CUA) to explore and quantify the cost per health (or utility) gain. The primary measure of effectiveness for CEA will be presented as the incremental cost-effectiveness ratio (ICER), defined as the additional cost per participant achieving an improvement in urinary incontinence over a 1-year period. The SF-6D measure of health-related quality of life will be used to calculate utility scores for the estimation of quality-adjusted life years (QALYs) for the CUA. Derivation of the SF-6D is from item responses on the SF-12 questionnaire, a generic health- related quality of life measure, across 6 dimensions: physical functioning, role limitations due to physical health, bodily pain, vitality, social functioning, role limitations due to emotional problems, and mental health [38]. The QALY is a measure of a participant’s life expectancy, weighted by their health-related quality of life, valued on a self-reported utility score, where a score of 1 reflects perfect health and 0 is equivalent to dead [38]. The incremental cost per QALY gained will be estimated at 1 year post intervention and will be depicted in a cost-effectiveness analysis decision tree. The SF-12 questionnaire will be administered at baseline and at 6-months and 12-months post intervention, while the cost questionnaires will be administered at 3-month, 6-month, 9-month and 1-year follow-up to the study participants (Table 1).

### Sample size

The sample size calculations were not equivalent for all the co-primary outcomes of the study and, therefore, differ based on the various outcomes.

We hypothesize that the sample size required to demonstrate the effectiveness of the continence promotion intervention will be sufficient as it is powered to detect a minimally clinical important difference of 20 % in the proportion of participants globally rating their improvement in urinary symptoms as “much better” or “very much better,” with an expected change in the control group of 6 % [39]. As the design is a cluster randomized trial, we need to adjust for both the clustering and the effect of unequal cluster sizes [40]. Based on the results from the pilot study [26], an estimated average cluster size of 4 participants and an intra-class correlation coefficient (ICC) of 0.02, we would require a minimum of 14 community organizations per arm (a minimum of 56 participants per arm) to be able to detect a difference of 20 %, with 80 % power and alpha 0.05. To account for attrition, which we estimate to be around 15 %, we decided to set the recruitment target to at least 100 participants per arm.

The sample size needed for the falls outcome anticipates an average baseline fall rate per group of 30 % [26], and hypothesizes that the intervention will have an effect on the incidence rate of falls of 0.21 (30 % relative reduction). A minimum sample size of 388 per group (at least 97 community organizations per group) is needed to detect this minimally important difference with 80 % power, 5 % level of significance, an ICC of 0.02 and an average cluster size of 4.

Sample size for the economic analysis was calculated using a mapping exercise to convert a minimally important difference on the I-QOL to the SF-12 to account for the possibility that the SF-12, a generic quality of life measure, may be insufficiently sensitive to reflect important differences in incontinence-related quality of life [39]. An improvement of 6.65 points on the I-QOL scale best matched an improvement (as much better or very much better) on the PGI-I, which we defined as a minimally important difference. Then, using a Monte Carlo simulation, we calculated that using this change cut-off, a detectable difference of 4.74 on the I-QOL between the intervention and control groups, would be statistically significant (at 0.05 alpha level) in at least 80 % of simulations when each group comprises at least 500 participants, representing a gain of 0.0126 in SF-6D utility scores.

Taking into account the sample size calculation for all co-primary outcome measures, we therefore aim to recruit the participants according to the largest sample size that will be sufficient for sub-group analyses (*n* = 500 participants per group) – a total of 1000 participants.

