**Methods:**

This study is a mixed methods multi-national open-label 2-arm parallel cluster randomized controlled trial aiming to recruit 1000 community-dwelling incontinent women aged 65 years and older across Quebec, Western Canada, France and United Kingdom. Participants will be recruited through community organizations. Data will be collected at 6 time points: baseline and 1 week, 3 months, 6 months, 9 months and 12 months after baseline. One of the primary objectives is to evaluate whether the continence promotion intervention improves incontinence symptoms (measured with the Patient Global Impression of Improvement questionnaire, PGI-I) at 12 months post intervention compared to the control group. Other co-primary outcomes include changes in incontinence-related stigma, fall reduction, and incremental cost-effectiveness ratio and quality-adjusted life years. Data analysis will account for correlation of outcomes (clustering) within community organizations. A qualitative sub-study will explore stigma reduction.

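### The 500 women per group that set the trial size are both the number needed for 80 % power on the I-QOL and the number to be recruited, so the protocol's own 15 % attrition would take that power to about 73 %

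*Protocol article*

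**What the plan says.** The Sample size section derives three numbers per group.

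- **PGI-I:** 56, from 14 organizations of about 4 women each, with an ICC of 0.02. Attrition is put at around 15 %, and in response "we decided to set the recruitment target to at least 100 participants per arm".
- **Falls:** 388, with the same ICC and cluster size. No attrition step is described.
- **Economic analysis:** the target is "a detectable difference of 4.74 on the I-QOL between the intervention and control groups", significant at the 0.05 level in at least 80 % of runs "when each group comprises at least 500 participants, representing a gain of 0.0126 in SF-6D utility scores".

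The section closes: "we therefore aim to recruit the participants according to the largest sample size that will be sufficient for sub-group analyses". That number is 500 per group, 1000 in total. The Methods paragraph of the abstract likewise describes the trial as "aiming to recruit 1000 community-dwelling incontinent women aged 65 years and older".

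The section also says that the cluster design calls for adjustment for clustering and for unequal cluster sizes. The text on the 500 mentions neither clustering nor attrition. Table 1 (under Outcomes) schedules the I-QOL at baseline, 6 months and 12 months. The Co-primary outcomes part of Data analysis compares I-QOL subscale scores between arms with women clustered by organization, and names no time point.

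**The concern.** A simulation result stated for groups of a given size refers to the women who enter the comparison. A recruitment target refers to the women who start. The protocol separates the two for the PGI-I, where the requirement is smallest, and equates them for the figure that decides how large the trial is. With losses at the protocol's own rate, the comparison would have fewer than 500 women per group and less than the stated power.

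The 4.74 points and the matching utility gain of 0.0126 both appear in the Study hypothesis, and quality of life with stigma is a co-primary outcome. A reader who meets an inconclusive I-QOL result would judge it against 80 % power, although the protocol's retention assumption implies less.

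**Working it through.** **Inputs (Sample size section unless noted)**

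- Difference 4.74 points; power at least 80 % at 500 per group; alpha 0.05, taken as two-sided because the text does not say.
- Recruitment 500 per group; allocation 1:1 (Randomization).
- Attrition about 15 %, stated in the PGI-I paragraph.
- ICC 0.02 and average cluster size 4, stated for PGI-I and falls. Design effect = 1 + (4 − 1) × 0.02 = 1.06.

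**Step 1: how the protocol's other figures were built.** The usual two-proportion formula was used, two-sided 0.05, 80 % power.

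- PGI-I, 6 % against 26 %: 52 per group; 52 × 1.06 = 55.1; rounded up to 14 clusters of 4, this is 56. Reproduced.
- Falls, 30 % against 21 %: 367 per group; 367 × 1.06 = 389, against 388 stated. Reproduced to within one.

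So the 56 and the 388 contain the design effect and no attrition.

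**Step 2: calibrating the I-QOL figure.** The 500 cannot be reproduced independently, because no SD or simulation input is given. Taking power as exactly 80 % at 500 analysed per group, the standardized effect at that size is 1.960 + 0.842 = 2.802. The implied SD is 4.74 / (2.802 × √(2/500)) = 26.75, but it drops out of what follows. For a fraction f of the 500 that is effectively available:

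- power = Φ(2.802 × √f − 1.960)
- difference detectable at 80 % power = 4.74 / √f

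**Step 3: attrition only.** 500 × 0.85 = 425, so f = 0.85.

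- Power = Φ(2.802 × 0.922 − 1.960) = Φ(0.623) = 73.3 %.
- Detectable difference = 4.74 / 0.922 = 5.14 points.

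**Step 4: attrition and clustering, if the simulation had neither.** 425 / 1.06 = 400.9, so f = 0.802.

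- Power = Φ(2.802 × 0.895 − 1.960) = 70.8 %.
- Detectable difference = 4.74 / 0.895 = 5.29 points.
- If losses shrink clusters to 4 × 0.85 = 3.4, the design effect is 1 + 2.4 × 0.02 = 1.048 and power is 71.3 %.

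**Step 5: sensitivity to the assumed loss**

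| Loss | Power, no design effect | Power, design effect 1.06 |
|---|---|---|
| 5 % | 78.0 % | 75.6 % |
| 10 % | 75.7 % | 73.3 % |
| 15 % | 73.3 % | 70.8 % |
| 20 % | 70.7 % | 68.2 % |

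With a one-sided alpha of 0.05, the two figures at 15 % loss are 74.1 % and 72.0 %.

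**Step 6: the other outcomes.** 425 is above both 388 (falls) and 56 (PGI-I).

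**The case against.** The best defence is that the simulation is only summarised. It may already have included dropout or clustering, and the text says at least 80 %, so there may be slack. This cannot be excluded, and it makes every figure here conditional. But nothing in the text points to it. Power at 500 would have to be about 86 % for 80 % to survive a 15 % loss (about 88 % with the design effect as well), while 500 is presented as the size at which 80 % is reached. The scaling also treats the test as a simple comparison of two means, although the simulation used a 6.65-point change cut-off and its test is not described.

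A second objection is that 15 % is given for the PGI-I and that all analyses are by intention to treat. The rate does have to be carried over. However, Table 1 collects the PGI-I and the I-QOL at the same 12-month telephone contact, so similar loss is a fair assumption. Intention to treat does not by itself supply scores that were not collected. What stands is that 425 applies to a 12-month comparison of women with data, which the analysis section does not expressly fix.

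A third objection concerns clustering, and most of it stands. The ICC of 0.02 is never stated for the I-QOL, and the pilot's intracluster correlation for symptom improvement was 0 (Background). The 71 % is therefore clearly more conditional than the 73 %. A reader might go lower still by allowing for unequal cluster sizes, but the article gives no measure of their spread, so no such figure can be supported.

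Finally, a reader might infer that the economic evaluation is underpowered. The documents do not support that: the Economic analysis section reports cost-effectiveness ratios, probabilistic sensitivity analysis and acceptability curves, not a significance test.

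**Conclusion.** The point holds, with moderate weight. The protocol gives one number two roles and leaves no stated margin for losses that it expects. Power for 4.74 I-QOL points is about 73 % (5.1 points detectable at 80 % power) on three assumptions: power is 80 % at 500 analysed per group, attrition was not simulated, and 15 % applies to the 12-month I-QOL. It is about 71 % (5.3 points) only if clustering was also left out of the simulation and the ICC of 0.02 with clusters of about 4 holds for this outcome.

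A reader might infer that the trial as a whole is too small. It is not shown to be: falls and PGI-I keep their required numbers. The point also changes no analysis, estimate or error rate. It concerns the stated power for the outcome that sets the trial size.

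**What to change.** In the Sample size section, restate the economic-analysis figure: with 500 recruited and about 425 analysed per group, power for a 4.74-point I-QOL difference is about 73 %, or about 71 % if clustering was not in the simulation. Alternatively, keep 80 % power and give the detectable difference as about 5.1 to 5.3 points. Say in the same sentence whether attrition and clustering were simulated; if either was, that part of the shortfall falls away.

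The cost is one restated figure, slightly less favourable than the present one. No extra recruitment is needed. For orientation only, preserving 80 % at 4.74 points would take 500 / 0.85 = 588.2, so 589 recruits per group, or 500 × 1.06 / 0.85 = 623.5, so 624 with the design effect.

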## Data analysis

### Co-primary outcomes

Differences in baseline characteristics between the groups will be determined using descriptive statistics (means, proportions), to assess any imbalance in potential confounders. All analyses will be done on an intention-to-treat basis. To assess improvements in incontinence, we will estimate the unadjusted risk difference (prevalence of the outcome) and 95 % confidence interval (CI) via generalized estimating equations (GEEs) with an identity link and an exchangeable correlation structure to account for possible correlation between women in the same organization [41]. The effects of various potential confounders in the groups at baseline will be explored because of the possibility for selection bias in an open trial. To adjust for imbalance in potential confounders, additional analyses will be conducted using multivariate logistic regression estimated via GEE with an exchangeable correlation structure. As a sensitivity analysis, we will repeat the analysis on a per protocol basis that will include participants who adhered to the protocol and follow-ups.

Incontinence-specific quality of life will be assessed using the Incontinence Quality of Life Instrument (I-QOL). The 22 items in the I-QOL will be summed and then transformed to a 0 to 100 scale for greater interpretability, with the higher scores representing greater quality of life. The I-QOL subscales (avoidance or limiting behaviors, psychological impacts, social life impact, and social embarrassment) will be scored in an identical manner. In an ad hoc analysis, crude effect sizes, examining change in scale scores at each assessment within participant group (intervention and control), will be calculated and evaluated using Cohen’s *d* criteria (i.e., 0.2–0.49 is small, 0.5–0.79 is moderate, and 0.8 and above is large). Multivariate linear models will be used to compare each I-QOL subscales score reported by the intervention group to the control group, with the control group as the referent and participants clustered by organization. Age at baseline and other potential confounders will be included as covariates in all adjusted models.

Fall rates in the intervention and the control groups will be analyzed as follow: (1) the incidence rate of falls, using Poisson regression to allow for clustering of falls by the same participant, (2) the proportion of patients who had one or more falls versus no falls, using logistic regression analyses, and (3) the proportion of injurious falls, using logistic regression analyses. Each analysis will use patient-level data that will be clustered by organization and analyzed via GEE with an exchangeable correlation structure and a log and a logit link for Poisson and logistic regression analyses respectively. Negative binomial regression will be used to model the incidence rate of falls, if there is evidence of over-dispersion of the data using Poisson regression. Multivariate analyses will adjust for any confounding variables that may affect the relationship between incontinence and falls.

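### The PGI-I co-primary analysis is fixed as unadjusted, without the site stratum or a collected baseline score, and the supportive adjusted models follow observed imbalance on another scale; the primary result stays valid but the plan gives up easy gains

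*Protocol article*

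**What the plan says.** All references are to the protocol article.

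- **PGI-I analysis** (Data analysis, Co-primary outcomes): "we will estimate the unadjusted risk difference (prevalence of the outcome") by GEE "with an identity link and an exchangeable correlation structure to account for possible correlation between women in the same organization". Organization is the only grouping in the model.
- **Randomization** (Randomization/Concealment of allocation): "we will randomly allocate clusters (via a 1:1 ratio and stratified by site) to the intervention or control group". The stated purpose is: "Stratification by site will aim to account for any variation resulting from site characteristics". There are four sites.
- **Baseline data** (Outcomes, Table 1): ICIQ-FLUTS, I-QOL and SF-12 are ticked at baseline. PGI-I and the falls diary are not.
- **Adjusted PGI-I models** (Co-primary outcomes): baseline characteristics are compared "to assess any imbalance in potential confounders", and then "To adjust for imbalance in potential confounders, additional analyses will be conducted using multivariate logistic regression estimated via GEE with an exchangeable correlation structure".
- **I-QOL models** (same section): linear models clustered by organization. "Age at baseline and other potential confounders will be included as covariates in all adjusted models". Neither site nor baseline I-QOL is named.
- **Falls models**: the multivariate analyses leave the list of confounders open.

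**The concern.** Stratifying by site removes site differences from the arm comparison by design. The analysis takes credit for that only if site is in the model; otherwise between-site variation stays in the estimated standard error. The stated purpose of the stratification is therefore not carried into the PGI-I model.

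The protocol also collects baseline scores likely to predict the outcomes and, for PGI-I, explicitly sets them aside. When adjustment does come, it is prompted by imbalance seen in the data, and it moves from a risk difference to a logistic model. A reader who sees the two results differ could not tell whether the covariates or the scale caused it.

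This matters more than usual here. The protocol itself gives possible selection bias in an open trial as its reason for exploring confounders, and its Limitations section concedes possible recruitment bias after randomization. Readers will look to the adjusted result, which is the less firmly specified one.

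**Working it through.** **1. The protocol's PGI-I sample size reproduces.** Inputs from Sample size: 6% v 26%, 80% power, alpha 0.05 (two-sided assumed), cluster size 4, ICC 0.02.
- Design effect: 1 + (4 − 1) × 0.02 = 1.06.
- n = [1.96·√(2 × 0.16 × 0.84) + 0.8416·√(0.06 × 0.94 + 0.26 × 0.74)]² / 0.20² = 51.6, so 52 per arm.
- 52 × 1.06 = 55.1, or 14 organizations of 4 = 56 per arm, as stated.

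The same method gives power of 81% at 56 per arm, 97% at 100 per arm, and above 99.9% at 425 per arm (500 less 15% attrition).

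**2. Scale.** Risk difference: 0.26 − 0.06 = 0.20. Odds ratio: (0.26/0.74) / (0.06/0.94) = 5.50.

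**3. Site and baseline score in the PGI-I model.** The protocol gives no between-site spread, so a range was assumed. The simulation used 125 organizations of 4 women per arm, four sites, 6% v 26% and organization-robust standard errors. The baseline score was given an assumed log-odds of 0.3 to 1.0 per SD.

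| Between-site SD (logit, assumed) | Fall in estimated variance: site added | Fall: site + one baseline score |
|---|---|---|
| 0 | about 1% | 2–10% |
| 0.3 | 4–5% | 6–13% |
| 0.6 | 12–14% | 15–20% |
| 1.0 | 24–28% | 29–30% |

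The true spread of the estimate was practically the same with and without site (for example 0.0212 in both at SD 1.0). What changed was the reported standard error: 0.0262 unadjusted against 0.0222 with site in that case, and 0.0222²/0.0262² = 0.72. Coverage of the unadjusted 95% interval was about 99% at SD 1.0 and close to or above 95% elsewhere. The error is in the conservative direction.

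**4. I-QOL power.** Sample size gives 80% power at 500 per group for a difference of 4.74. It does not say whether that simulation allowed for attrition, clustering or baseline adjustment. Assume that it allowed for none of them.
- At 80% power the standardized effect is 1.96 + 0.8416 = 2.8016.
- With 425 per arm and design effect 1.06: power = Φ(2.8016·√(0.85/1.06) − 1.96) = Φ(0.549) = 71%.
- With baseline adjustment: power = Φ(2.8016·√(0.85/(1.06·k)) − 1.96). Against a post-score analysis k = 1 − r². Against change scores k = (1 − r²)/[2(1 − r)] = (1 + r)/2.

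| r (assumed) | Power, against post-score | Power, against change score |
|---|---|---|
| 0.3 | 75% (k = 0.91) | – |
| 0.5 | 83% (k = 0.75) | 83% (k = 0.75) |
| 0.6 | 88% (k = 0.64) | 80% (k = 0.80) |
| 0.7 | – | 78% (k = 0.85) |

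If the 500 per group already covers attrition and clustering, but not baseline adjustment, the start is 80%. Power then becomes 84%, 90% and 94% at r = 0.3, 0.5 and 0.6 against a post-score analysis.

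**The case against.** The best defence is that the PGI-I primary analysis is sound as written. It is fully fixed in advance and its interval is at worst conservative. A reader might infer that leaving out the stratum inflates type I error or endangers the PGI-I conclusion. Neither follows: the error makes the interval too wide, only if sites differ, and power is above 99.9%. This part of the defence stands.

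A reader might also infer that covariate choice after the fact contaminates the primary result. It cannot, because the imbalance-driven models are described as additional. Age is also named for the adjusted models, so the choice is not wholly open. This stands too.

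On I-QOL, the protocol's wording leaves room for other potential confounders and does not exclude baseline I-QOL or site. A full covariate list may sit in an analysis plan that is not shown. So it would be wrong to say that the protocol has decided to leave the baseline score out, and the power figures are conditional on that and on an assumed correlation.

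Finally, a logistic GEE can yield a risk difference by standardization, and the protocol does not say that only odds ratios will be reported. That softens the scale point, but no common scale is stated.

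The defence does not remove three things that the text does fix: an unadjusted PGI-I model despite site stratification, adjustment triggered by observed imbalance, and an adjusted PGI-I model of a different form from the primary one.

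**Conclusion.** The point holds as an improvement to a valid analysis, not as a flaw that invalidates it.

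For PGI-I, adding site would lower the estimated variance of the risk difference by about 1% to 28% over an assumed between-site logit SD of 0 to 1.0. PGI-I power is not threatened.

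For I-QOL the gain could matter, because that outcome sets the trial's size. It depends on the basis of the 80% figure, which is not stated, and on a correlation that the protocol does not give. A reader might conclude that baseline adjustment is sure to restore 80%. It does not at r = 0.3 against a post-score analysis (75%) or at r = 0.7 against change scores (78%). Nor is most of the precision lost: for r between 0.5 and 0.6 the variance saved is 25–36% against post-scores and 20–25% against change scores.

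Imbalance-driven selection affects the supportive PGI-I models only, but in this open trial those models will be read closely.

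**What to change.** Before the blinded statistician sees allocation, prespecify the covariates of each co-primary model:

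- **PGI-I:** arm, site (4 levels), age and baseline ICIQ-FLUTS. PGI-I is a rating of change and has no baseline value of its own.
- **I-QOL:** arm, site, age and baseline I-QOL.
- **Utility:** arm, site, age and baseline SF-6D.
- **Falls:** arm, site and age. The falls diary has no baseline entry, and the protocol gives no basis for another score here.

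Report the adjusted PGI-I result as a risk difference, standardized from the logistic GEE with organization-robust errors. Keep the unadjusted difference as supportive. Drop covariate selection by observed imbalance; the baseline table can remain descriptive. State whether the I-QOL simulation allowed for attrition, clustering and baseline adjustment.

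The cost is wording, slightly more analysis work and a few degrees of freedom. No new data are needed. With recruitment about 60% complete at submission (Trial status), there was still time to settle this in advance. Adjustment for measured covariates will not by itself cure recruitment bias in sites where consent follows the workshop.
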